## Abstract

**Background:**

Studies in bipolar disorder (BD) to date are limited in their ability to provide a whole-disease perspective - their scope has generally been confined to a single disease phase and/or a specific treatment. Moreover, most clinical trials have focused on the manic phase of disease, and not on depression, which is associated with the greatest disease burden. There are few longitudinal studies covering both types of patients with BD (I and II) and the whole course of the disease, regardless of patients' symptomatology. Therefore, the Wide AmbispectiVE study of the clinical management and burden of Bipolar Disorder (WAVE-bd) (NCT01062607) aims to provide reliable information on the management of patients with BD in daily clinical practice. It also seeks to determine factors influencing clinical outcomes and resource use in relation to the management of BD.

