One of the key challenges in ensuring that a new study produces meaningful data is to avoid any selection bias in recruitment of both investigators and patients. This can be achieved by having as few exclusion criteria as possible. A further challenge is to recruit patients without contravening the diverse range of laws, which vary within and between countries, covering privacy relating to the acquisition and use of medical data. A recent study in another area of medicine has attempted to avoid investigator bias in patient selection by engaging a third party to manage patient selection and recruitment [11]. In that study, patients were able to opt out without consulting their physician.

In view of the above, the overall objectives of the Wide AmbispectiVE study of the clinical management and burden of Bipolar Disorder (WAVE-bd) study are: to provide accurate and reliable information on the management of patients with BD in conditions representative of everyday clinical practice; to determine the clinical outcomes of such management and the use of resources in relation to the disease; and to establish the factors associated with different management patterns and clinical and functional outcomes.

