**Figure 1 F1:**
[figure not shown]
**Study design**.

The study comprises two different follow-up phases; one retrospective and one prospective (ambispective design). The retrospective phase for each patient started from the index event, which occurred a maximum of 12 months and minimum of 3 months before Time 0, and ended when the patient signed the informed consent form. Information from medical records related to the patient and their disease during that period (i.e. retrospective information - from index event to inclusion) was recorded in the electronic case report form (eCRF) at the inclusion visit. The prospective phase started when the first patient signed the informed consent form and will end when the last patient included in the study attends their final visit. Data for prospective analysis are collected as described at all visits (including the inclusion visit). All throughout the prospective phase, the required information will be recorded in the eCRF and the questionnaires completed every time the patient attends the psychiatrist's office (unless otherwise stated). The psychiatrist will schedule visits according to real-life clinical practice. No interventions, extra procedures, or extra visits will be required for the purpose of the study.

The study design means that patients will spend variable amounts of time in the study depending on the date of signing the informed consent form, the length of the enrolment period, and the date of their index episode. The minimum time in the study is 12 months and the maximum 27 months, considering the retrospective and prospective phases, and the 6 month enrolment period together (Figure 1).

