### Measurements

The WAVE-bd study aims to provide a wide-ranging picture of BD management practices, and impact on patients, caregivers and healthcare resource use across a range of countries. For this reason, several measuring instruments are being employed to maximise the types of data collected. All instruments have been validated before the study start, including linguistic validation where needed. In all cases, the scales were also psychometrically validated, at least in the original language. Information regarding demographics (sex, race, age, educational level, professional status, degree of disability, degree of independence or co-residence), alcohol and other substance abuse, medical history, disease characteristics (date of first diagnosis, type of BD, family history of psychiatric diseases, episodes during the last 12 months, presence of psychotic symptoms, hospital admissions, and suicide attempts), treatments received (drug, schedule and dose, and whether the patient received psychologist or group therapy), healthcare resources use, and clinical outcomes will be collected throughout the study (Table 2).

**Table 2 T2:** Study plan and assessments

Time	First visit*	Each other visit	Last visit
Site information	X		
Patient demographics	X		
Medical history	X		
Disease characteristics	X		
Treatment information	X	X	X
Healthcare resources consumption	X	X	X
Clinical outcomes	X	X	X
Adherence to treatment	X	X	X
Quality of life	X	X	X
Functioning	X	X	X
Caregiver demographics	X**		
Caregiver burden	X**		

* First visit: the visit when the patient signs the informed consent form.

** If the caregiver does not attend this visit, the information will be collected at the next visit that the caregiver attends. This information will be collected (if the caregiver consents) only once during the study period for each caregiver. In the event that the caregiver does not attend any visits, this information will not be collected.

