### Statistical analyses

Descriptive statistics will include frequency tables (n, mean, median, standard deviation, minimum and maximum for continuous variables and n, frequency and percentage for categorical values). For the population estimation of the variables, the two-sided 95% confidence interval will be obtained.

In order to assess the association of patient characteristics (including functioning and quality of life status) and clinical management (an independent variable) with clinical outcome variables (clinical evolution, mood events, treatment-related events, suicide attempts, variation in scales), logistic and general linear models have been planned. Interest will focus separately on the management differences between the models or groups of models. Model-based point estimates of odds ratios and corresponding 95% confidence intervals will be reported. P-values will be reported for the comparison between different treatments. Since visit-by-visit information from the study index event is being collected, there will be data on patient status during the whole study period. Therefore, it will be possible to analyse data, relative to the time of mood event initiation.

Cox models for survival outcomes, and mixed models for longitudinal data using country as indicator variables, adjusted for age and gender, have been planned in order to investigate differences in clinical outcomes and related factors between countries. A descriptive analysis has been planned to assess factors related to consumption of healthcare resources and caregiver burden, according to caregiver-reported outcomes.

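### Factors related to resource use get only a descriptive analysis, with no adjustment or person-time denominator stated, although follow-up is unequal by design and site type is tied to country

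*Protocol article*

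**What the plan says.** The Protocol article describes the place of resource use in three ways.

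- **Abstract, Background:** "It also seeks to determine factors influencing clinical outcomes and resource use in relation to the management of BD". Clinical outcomes and resource use share one aim here.
- **Background, closing paragraph (objectives):** the study is "to determine the clinical outcomes of such management and the use of resources in relation to the disease". The next clause, on associated factors, names management patterns and clinical and functional outcomes. It does not name resource use.
- **Methods, Statistical analyses:** "A descriptive analysis has been planned to assess factors related to consumption of healthcare resources and caregiver burden". For clinical outcomes the same section plans logistic and general linear models, Cox models, and "mixed models for longitudinal data using country as indicator variables, adjusted for age and gender".

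Three design features bear on this.

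- **Study design:** "patients will spend variable amounts of time in the study", and "The minimum time in the study is 12 months and the maximum 27 months". Visits are not fixed: "The psychiatrist will schedule visits according to real-life clinical practice".
- **Sites and investigators:** the article accepts that site type may affect management and that patient profiles may differ between site types. Table 1 gives the site mix by country.
- **Table 2 footnote and the description of the Burden Assessment Scale (BAS):** caregiver burden is measured once per caregiver. If the caregiver misses the first visit, "the information will be collected at the next visit that the caregiver attends". If no caregiver ever attends, nothing is recorded.

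**The concern.** The Statistical analyses section sets out to assess factors for resource use, and the abstract calls this determining influences. The named method is weaker than the one for clinical outcomes, and nothing in the text says how observation time, country or site type will be handled.

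Resource use accumulates with time under observation, and it plausibly depends on the care setting. If factors are compared on raw totals or on percentages with any use, a characteristic that is more common in patients observed longer, or in countries that recruited mainly through hospitals, can look like a driver of resource use when it is not. The Discussion promises a cross-country comparison of resources used, so these tables are likely to be read that way.

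Caregiver burden shares the descriptive plan but raises a different issue. The single BAS score may be taken at different times since the index event and in different illness states, and only for patients whose caregiver attends and consents.

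**Working it through.** The plan gives no figure for resource use. The check therefore uses the follow-up limits (Study design) and the Table 1 counts.

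**1. Observation time.** With an identical constant rate, the ratio of expected raw totals for two patients is the ratio of their observed months.

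| Months compared | Ratio of raw totals |
|---|---|
| 27 vs 12 (design extremes) | 27/12 = 2.25 |
| 24 vs 15 | 24/15 = 1.60 |
| 21 vs 18 | 21/18 = 1.17 |

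Percentages with any use also shift. The documents give no resource-use rates, so the rates here are assumptions. With a constant Poisson rate r per year and t years observed, P(any) = 1 − exp(−r·t), with t = 1 or 27/12 = 2.25.

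| Assumed r per year | 12 months | 27 months |
|---|---|---|
| 0.5 | 39% | 68% |
| 1 | 63% | 89% |
| 2 | 86% | 99% |

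Under the same assumption, the rate per patient-year is equal in both groups, so a person-time denominator removes the difference.

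**2. Site type and country.** Table 1's counts sum to 2965, the number of consenting patients given in the Discussion. The share recruited at sites labelled private practice is the private-practice count divided by the country total.

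| Country | Count / total | Share |
|---|---|---|
| Brazil | 0/166 | 0% |
| Romania | 0/183 | 0% |
| Ukraine | 22/221 | 10% |
| Belgium | 129/414 | 31% |
| Venezuela | 76/231 | 33% |
| Turkey | 151/383 | 39% |
| France | 260/507 | 51% |
| Germany | 114/219 | 52% |
| Portugal | 295/516 | 57% |
| Austria | 81/125 | 65% |

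Where Table 1 prints a private-practice percentage, these shares agree with it. Two limits follow. Labels differ between countries (Romania lists ambulatory and hospital sites, for example), so the shares depend on labelling. All Brazilian patients come from hospitals (146 public, 20 university), so Brazil offers no hospital versus non-hospital contrast. A crude comparison by site type carries country with it, and the reverse.

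**3. Caregiver burden.** BAS is one score, so step 1 does not apply to it. What can vary is when it is taken, the patient's state at that visit, and whether it is taken at all.

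**The case against.** The strongest reply is that descriptive does not mean crude. A descriptive analysis can use rates per patient-year and stratify by country and site type, and an article may leave such detail to the full protocol or SAP, which are not shown. The article also points towards stratification: it foresees comparisons of public with private care and of hospital with non-hospital care. This stands against any claim that the tables will be confounded or that the study cannot answer its question. It does not remove the point. The article itself fixes the type of analysis for resource-use factors, and fixes a different one for clinical outcomes.

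A second reply is that resource-use factors are not a main objective, because the closing objectives omit them. That also stands, so it would be too much to call them co-equal with clinical outcomes. But both the abstract and the Statistical analyses section do refer to such factors, so the sections still disagree.

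A third reply concerns size. A reader might take 2.25 as the expected bias, or apply it to differences between countries. Neither is supported. It is the ratio for raw totals at the two design extremes. Group means would usually differ far less, and nothing in the article shows that follow-up differs by country.

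Finally, the site imbalance limits the remedy too, because a model with both country and site type can separate them only where they overlap.

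**Conclusion.** The concern holds in a limited form. The article means to assess factors for resource use but names only a descriptive analysis, without a stated adjustment or person-time denominator. Its closing objectives do not list that aim. With 12 to 27 months of observation and private-practice shares from 0% to 65% across countries, crude factor comparisons of resource use are open to confounding.

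The size of any actual bias cannot be derived from the document. The ratios of 1.17 to 2.25 assume equal constant rates and raw totals, and they matter only if the factor is related to length of observation. The percentages with any use also rest on assumed contact rates.

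A reader might infer that longer follow-up inflates caregiver burden. It does not, because BAS is measured once and does not accumulate. Only its timing, the patient's concurrent state and missing caregiver data are at issue.

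This should be put right before analysis. It does not undermine the design.

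**What to change.** **Preferred change, in Statistical analyses:**

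- Keep the descriptive tables, but express resource use per patient-year, by country and by site type.
- Add a count regression (for example negative binomial) for admissions, visits and similar counts. Use log observed time as offset, with country, site type under a harmonised classification, age, sex and BD type as covariates. State that country and site type overlap only partly, so their separate effects rest on the countries with mixed sites.
- Model hospital days only if they are recorded. The Measurements section names admissions and resource use but not days.
- For BAS, adjust for country, site type, time of assessment and, where available, the CGI-BP rating from the same visit. Report the share of patients without caregiver data.

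**Alternative:** restate the resource-use aim as descriptive, so that the abstract, the closing objectives and Statistical analyses agree, and report rates per patient-year by country and site type.

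**Cost:** wording, one recoding of site types and modest extra analysis. Table 2 already schedules site information, demographics and disease characteristics at the first visit, and resource use and clinical outcomes at every visit, so the core model needs no added visits or data.

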### Sample size

The sample size was calculated in order to ensure that the study obtains meaningful data for descriptive purposes of general clinical management and clinical outcomes at a country level. The main outcome used in the sample size calculation was the proportion of episodes in 1.5 years and the goal was to estimate this proportion in the study population. The minimum number of patients required was estimated, based on an expected proportion of patients with episodes in one year of 35%, assuming an alpha = 0.05, power = 0.80 and a precision of 0.05 (with a 95% confidence interval). The estimated sample size was 370 patients per country (or 400 if it is assumed that approximately 10% will be lost to follow up). Fewer patients per country would provide information on the proportion of episodes with a precision less 5%. It was estimated that approximately 3,200 patients across different countries would be included in the study, but that this number might vary depending on the number of participating countries and sample size in each.

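### The sample size paragraph sets a 1.5-year outcome against a one-year rate, quotes a power that nothing uses, and under-inflates 370 for 10% loss; the effect on precision is small

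*Protocol article*

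**What the plan says.** All the sizing statements are in the Sample size section of the protocol article.

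- Outcome: "The main outcome used in the sample size calculation was the proportion of episodes in 1.5 years". The stated goal is to estimate that proportion in the study population.
- Planning value and error rates: "based on an expected proportion of patients with episodes in one year of 35%, assuming an alpha = 0.05, power = 0.80".
- Precision: "a precision of 0.05 (with a 95% confidence interval").
- Result: "The estimated sample size was 370 patients per country (or 400 if it is assumed that approximately 10% will be lost to follow up").

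No interval formula is named. The Statistical analyses section says that, for population estimates, "the two-sided 95% confidence interval will be obtained".

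**The concern.** Three things in this short paragraph do not fit together.

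1. **Horizon and unit.** The outcome runs over 1.5 years, but the rate used to size it runs over one year, and no conversion is given. The outcome is worded as a proportion of episodes and the planning value as a proportion of patients with episodes. A reader cannot tell which quantity the ±5 points belongs to. The ambiguity is practical: the Study design section allows a total time in study of 12 to 27 months, so some patients may be observed for one year but not for 1.5.
2. **Power.** A precision calculation for one proportion has no power term. No null value, difference or hypothesis is stated. The Statistical analyses section plans p-values for treatment comparisons and models for differences between countries, so a stray 0.80 could be taken to cover those.
3. **Loss to follow-up.** Taking 10% off 400 leaves fewer than the 370 that the section calls the minimum.

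**Working it through.** **Inputs.** From Sample size: p = 0.35 (one year), half-width d = 0.05, 95% interval, stated n = 370, stated gross n = 400, loss about 10%. From Statistical analyses: two-sided, so z = 1.96. No 1.5-year proportion is given anywhere, so any such value below is an assumption.

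**Step 1: reproduce 370.**

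- Uncorrected (Wald): n = z²p(1−p)/d² = 1.96² × 0.35 × 0.65 / 0.05² = 349.6, so 350.
- Continuity-corrected: the smallest n with z√(p(1−p)/n) + 1/(2n) ≤ 0.05. At n = 369 the left side is 0.05002 (fails); at n = 370 it is 0.04860 + 0.00135 = 0.04995 (passes). So n = 370, an exact match.
- Exact (Clopper-Pearson), by mean half-width: 367.

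The stated 370 follows from the stated one-year inputs with a standard correction.

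**Step 2: does power enter?** Step 1 gives 370 without it. Two calculations in which 0.80 would have a role do not give 370:

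- A one-sample test of 35% against a value 5 points away, with 80% power, needs about 698 (against 30%) or 726 (against 40%).
- An 80% chance that the uncorrected half-width is at most 0.05 needs 359.

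**Step 3: loss to follow-up.** 370 / 0.90 = 411.1, so 412. Conversely 400 × 0.90 = 360.

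| Method, p = 0.35 | Net n for ±5 points | Gross n at 10% loss | Half-width at 360 |
|---|---|---|---|
| Continuity-corrected | 370 | 412 | 4.93 + 0.14 = 5.07 points |
| Uncorrected | 350 | 389 | 4.93 points |

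With the corrected method the net figure matches but 400 is too low. With the uncorrected method 400 is enough but 370 is not the answer. Neither method gives both figures.

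**Step 4: move the rate to 1.5 years.** Assuming a constant hazard, p = 1 − 0.65^1.5 = 0.476.

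| Method, p = 0.476 | Half-width at 370 | Evaluable n for ±5 points |
|---|---|---|
| Uncorrected | 5.09 points | 384 |
| Continuity-corrected | 5.09 + 0.14 = 5.22 points (before rounding, 0.05089 + 0.00135 = 0.05224) | 404 |

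**Step 5: how far does Step 4 depend on the assumption?** Over an assumed 1.5-year proportion of 0.38 to 0.525, the uncorrected requirement is 363 to 385, and the uncorrected half-width at 370 is 4.9 to 5.1 points. Because p(1−p) peaks at p = 0.5, the uncorrected half-width at 370 cannot exceed 5.09 points for any proportion. Adding 1/(2 × 370) = 0.14 points gives a ceiling of about 5.23 for the corrected one.

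**The case against.** The best defence is that nothing of consequence turns on this. The 370 is correct for the one-year inputs. The section says loss is only approximately 10%, and 400 is within 3% of 412. The section declares a descriptive purpose, so the power figure is a superfluous phrase. The constant-hazard value of 47.6% is not in the documents. Realised precision depends on actual enrolment, which Table 1 puts at 125 in Austria (20 + 81 + 24) and 516 in Portugal (123 + 295 + 98). At p = 0.35 these give uncorrected half-widths of about 8.4 and 4.1 points, a far wider spread than 370 against 384 could produce.

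Most of that stands on size. It does not remove the textual conflict over what is being estimated, nor does it give the power figure a meaning. Rounding explains little of the loss point: going from 370 to 400 allows for 30/400 = 7.5% loss, and the section calls 370 a minimum.

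Three stronger readings are tempting, and the documents do not support them:

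- **That 370 is an arithmetic error and should be 350.** The section names no formula. 350 is only the uncorrected variant, and the corrected one gives 370 exactly. An article that does not name its formula is condensing, which is no fault.
- **That the study fell short of a promised 80% power for country or treatment comparisons.** No such promise is made. The calculation is for estimating one proportion. The fault is a number without a referent, which a reader might misapply.
- **That ±5 points is badly missed at 1.5 years.** Step 5 caps the excess at about 0.1 point uncorrected, or 0.23 corrected.

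**Conclusion.** The point holds as a defect of statement with a small numerical effect. The sizing paragraph uses two horizons and two units for one outcome, and it quotes a power that the calculation does not use. On the method that reproduces 370, the gross figure is about 12 patients per country short (412 against 400), which means 5.07 rather than 5.00 points. At 1.5 years, 370 evaluable patients give about 5.1 points uncorrected or 5.2 corrected if the hazard is constant. If the 1.5-year proportion is lower, as it would be if risk falls with time, the half-width is smaller.

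Two things here are inferred. The continuity correction is inferred because it matches 370 exactly. The 1.5-year proportion is assumed, with the range shown. The one-year/1.5-year conflict, the change of unit and the unused power figure depend on neither. Severity is minor to moderate: no planned analysis changes, but the text should not leave the main sizing outcome ambiguous.

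**What to change.** Restate the Sample size paragraph as follows.

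- Use one horizon and one unit throughout: the proportion of patients with an episode.
- Delete the power figure.
- If one year is meant, define the outcome at one year, keep 370 and give the gross figure as about 412.
- If 1.5 years is meant, state the assumed 1.5-year proportion and its basis, and report the precision that 370 delivers. Under a constant hazard that is about 5.1 points (uncorrected) or 5.2 (corrected), and ±5 points would need 384 or 404 evaluable patients.
- Naming the interval method would help the reader reproduce the figure.

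The cost is text only. Recruitment is complete (2965 consented, according to the Discussion), so no patients are added. The 370 should stay on record as the figure planned and should not be replaced by 350.

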### Sites and investigators

Since the type of site is a variable that might influence the management of patients with BD and the profile of patients attending each type of site may be different, it was necessary to select different types of sites to obtain a representative sample. Generally, patients with BD are seen in mental health centres, clinics, private settings, hospitals or specialised units. Since this distribution varies from one country to another, the study centre selection process had to be adapted locally.

Selection of participating sites was based on the percentage of patients that attend different types of sites in each country, thus ensuring that patients attending one specific site type are not over-represented in the study sample (Table 1). These percentages were obtained either from the literature or from expert panels from each participating country.

**Table 1 T1:** Patient recruitment by country and type of study centre

Country	Site type	Patients per site type (%)	Total patients enrolled
Austria	University hospital	16	20
	Private practice	65	81
	General hospital	19	24

Belgium	Clinics	46	190
	Private practice	31	129
	General practitioner	23	95

Brazil	Public hospital	88	146
	University hospital	12	20

France	Hospital/clinics	49	247
	Private practice	51	260

Germany	University hospital	27	59
	Community hospital	21	46
	Private practice	52	114

Portugal	Hospital	24	123
	Private practice	57	295
	Mental health clinic	19	98

Romania	Ambulatory	37	68
	Hospitals	63	115

Turkey	Private practice	39	151
	University hospital	42	162
	State hospital	18	70

Ukraine	Mental health clinic	90	199
	Private practice	10	22

Venezuela	Private practice	33	76
	Public hospital	67	155

The number of participating investigators is sufficient to ensure: 1) that there is a representative sample of the whole psychiatrist population in each country; and 2) inclusion of a sufficient number of patients to provide the required sample size calculated for the study. No other criteria were applied to selection and inclusion of investigators, in order to avoid any selection bias.

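### Six of the ten countries enrolled 34%–62% of the stated per-country minimum of 370, and the article does not give the wider country-level precision that results

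*Protocol article*

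**What the plan says.** The Sample size section gives the purpose as "meaningful data for descriptive purposes of general clinical management and clinical outcomes at a country level". It starts from an "expected proportion of patients with episodes in one year of 35" per cent, "assuming an alpha = 0.05, power = 0.80 and a precision of 0.05 (with a 95% confidence interval", and describes the result as the minimum number of patients required: "The estimated sample size was 370 patients per country (or 400 if it is assumed that approximately 10% will be lost to follow up".

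Two qualifications follow. The first is "Fewer patients per country would provide information on the proportion of episodes with a precision less 5" per cent. The second is about the total: "It was estimated that approximately 3,200 patients across different countries would be included in the study", with the remark that this could vary with the number of countries and the size of each.

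The Sites and investigators section says there are enough investigators to supply the calculated sample size. Table 1 in that section ("Patient recruitment by country and type of study centre") lists the patients enrolled by site type in ten countries. The closing discussion reports 2,965 consenting patients, so the table shows completed enrolment.

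**The concern.** The article prints a per-country minimum, a statement that the required size is provided for, and an enrolment table in which most countries miss that minimum. Nothing in the text connects the three. Country-level description is the declared reason for the sample size, so a reader needs to know how precise each country's estimate will be.

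The one sentence on smaller countries does not tell them. It has no number, names no country, and is conditional although the counts are already known. Because precision has just been defined as 0.05, a precision described as less than 5% can also be read as a narrower interval, when the interval is in fact wider.

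**Working it through.** **Inputs.** p = 0.35, half-width d = 0.05, two-sided 95% interval (z = 1.96), about 10% loss: Sample size and Statistical analyses sections. Enrolled numbers: Table 1, site types summed within country.

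**The plan's own figure.**
- Wald: n = z²p(1−p)/d² = 1.96² × 0.35 × 0.65 / 0.05² = 349.6, so 350. This does not give 370.
- Continuity-corrected: n/4 × (1 + √(1 + 2/(nd)))² with n = 349.6 gives 369.3, so 370. The shortcut n + 1/d = 369.6 also gives 370.

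The stated 370 is therefore reproduced with a continuity correction. The stated power of 0.80 plays no part in either formula. On loss, 370/0.9 = 411.1, so 412; the stated 400 leaves 360 evaluable, close to the target.

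**Country totals.** The Table 1 sums add to 2,965, which agrees with the discussion. Four countries reach 370 and three reach 400. The other six have 125/370 = 34% to 231/370 = 62% of the minimum.

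**Achieved half-width at p = 0.35, in percentage points.** Wald: 1.96√(0.35 × 0.65/n). Corrected: the same plus 1/(2n). After loss, n is replaced by 0.9n.

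| Country | Enrolled | Wald | Wald, 10% loss | Corrected | Corrected, 10% loss |
|---|---|---|---|---|---|
| Austria | 125 | 8.36 | 8.81 | 8.76 | 9.26 |
| Brazil | 166 | 7.26 | 7.65 | 7.56 | 7.98 |
| Romania | 183 | 6.91 | 7.28 | 7.18 | 7.59 |
| Germany | 219 | 6.32 | 6.66 | 6.55 | 6.91 |
| Ukraine | 221 | 6.29 | 6.63 | 6.52 | 6.88 |
| Venezuela | 231 | 6.15 | 6.48 | 6.37 | 6.72 |
| Turkey | 383 | 4.78 | 5.04 | 4.91 | 5.18 |
| Belgium | 414 | 4.59 | 4.84 | 4.72 | 4.98 |
| France | 507 | 4.15 | 4.38 | 4.25 | 4.49 |
| Portugal | 516 | 4.12 | 4.34 | 4.21 | 4.45 |

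Six countries miss 5 points before any loss, by either formula. Turkey meets it as enrolled and slightly exceeds it after loss. Belgium, France and Portugal hold it throughout. The six hold 125 + 166 + 183 + 219 + 221 + 231 = 1,145 patients, and 1,145/2,965 = 39%.

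**Planned total.** Ten countries at the stated minimum need 10 × 370 = 3,700, or 10 × 400 = 4,000 with loss. The planned figure is about 3,200.

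**The case against.** The strongest reply is that the article never promises 5 points in every country. It ties that precision to 370 patients, and its next sentence says that smaller countries will do less well. This stands. A reader might infer a blanket claim that enrolment then contradicts, but the text does not make one: the shortfall is foreseen in general terms, and Table 1 prints the numbers.

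It can also be said that a sentence opening with fewer patients can sensibly mean only lower precision. That is the likely intention, but the words still allow the opposite reading and give no size.

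The planned total is not shown to be wrong. The article does not say that 3,200 was meant for ten equal countries, and it says the number may vary. Since 3,200 = 8 × 400, it would fit a plan for eight countries, though that is an inference. What remains is that the figure has not been reconciled with the ten countries that took part.

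A reader might also conclude that modest differences between countries cannot be detected. These figures do not show that: half-widths of single proportions do not measure differences, and the Statistical analyses section compares countries through Cox and mixed models adjusted for age and gender.

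Finally, a precision table could be left to a fuller document. But the target, the statement on investigator numbers, the enrolled counts and the ambiguous sentence are all in this article, and they should agree with each other.

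**Conclusion.** The concern holds in a limited form. The calculation of 370 is not in error. The weakness is that a stated minimum for country-level precision is missed in six of ten countries and the article does not report the consequence. In those six the half-width is about 6.2 to 8.4 points by Wald (6.5 to 8.8 after loss), or about 6.4 to 8.8 with the continuity correction (6.7 to 9.3 after loss), against a target of 5.

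These sizes assume the plan's 35%, simple binomial sampling within each country and an equal 10% loss everywhere. The 35% is a one-year figure, while the sizing outcome is described as "The main outcome used in the sample size calculation was the proportion of episodes in 1.5 years". If the true proportion were nearer 50% (an assumption, and the worst case), the Wald range as enrolled would be about 6.4 to 8.8 points.

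This should be fixed, but it is not critical: no enrolment, estimand or analysis changes.

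**What to change.** 1. Add a table of achieved half-width per country from the Table 1 totals, before and after 10% loss, using the formula that produced 370, and name that formula. Mixing plain Wald figures with a continuity-corrected 370 would create a new inconsistency.
2. State that after loss 5 points is held only in Belgium, France and Portugal, that Turkey meets it as enrolled but is slightly above it after loss (5.04 Wald, about 5.2 corrected), and that the other six countries miss it.
3. Reword the sentence on smaller countries to say that fewer patients give a half-width larger than 5 points.
4. Qualify the statement in Sites and investigators that investigator numbers suffice for the required sample size, since in six countries the per-country figure was not reached.
5. State how many countries the 3,200 assumed, and note that ten countries at the stated minimum would need 3,700 to 4,000.

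The cost is one small table and a few sentences. No patients or analyses are added; the stated precision becomes less favourable.
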